
#### Secondary outcomes

The secondary outcomes evaluate older people’s experience of the exercise programmes. The measurements include exercise adherence, dropout rate, exercise maintenance, and Rosenberg Self-esteem Scale. Focus group interviews with open-ended questions will be conducted to evaluate the overall experience of older people with an emphasis on their psychological welfare, social well-being, and their acceptance of the telehealth approach.

Exercise adherence will be reflected by the attendance rate which is the percentage of exercise sessions attended by the participants during the 3-month intervention period.Dropout rate: This will be assessed by the number of participants who refuse to continue the training during the intervention phase or refuse to provide information during the maintenance phase. The details of the dropout will be recorded.Exercise maintenance: This will be measured by the Physical Activity Scale for the Elderly (PASE), weekly activity level and exercise diary of the participants at the baseline, and after 3, 6 and 12 months. PASE is a widely used questionnaire in epidemiological studies for assessing the physical activity level of older people. It comprises 12 items addressing the leisure, physical, household and work-related activities over the past week [34]. Physical activity level will be measured objectively by accelerometers (ActiGraph GT3X, Pensacola, FL, USA). The participants will wear one on their waist for seven consecutive days at the baseline, and 3rd, 6th and 12th months. Their total steps, activity energy expenditure, metabolic equivalent of task scores and physical activity levels will be estimated by the ActiLife software.Rosenberg Self-Esteem Scale: This is one of the widely used measures of self-esteem. The scale includes 10 items rated on a 4-point scale ranging from 1 (strongly disagree) to 4 (strongly agree), with higher scores indicating higher self-esteem.

### Adverse event reporting

Any adverse events during the intervention and maintenance phase will be recorded. The details of any adverse event such as the type, the time and the severity, will be recorded and analyzed to ascertain whether it is related to the study. In the case of a serious adverse event during the class, we will review the causes, the prescribed exercises, the course structure, and the safety precautions. The concerned participant will be suspended from the study. The data analysis and reporting of such adverse events will follow the CONSORT statement for better reporting of harm-related data [42].

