### Baseline assessment

The details of the study will be explained to all participants, who will sign the consent form. Assessment will be performed before the intervention period, at the end of the 3rd, 6th and 12th months. The baseline assessments include the Chinese version of Fall Efficacy Scale-International (FES-I), fall incidence, SARC- CalF scoring, right-hand and left-hand grip strength, Timed Up and Go test, Berg Balance Scale, 6-metre walk test, Functional Reach Test, Physical Activity Scale for the Elderly (PASE) [34], Daily activity level, Rosenberg Self-esteem Scale and EQ-5D-3 L. The weight, body fat and skeletal muscle mass will be measured by a bioimpedance scale.

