### Interventions

All participants will attend the exercise training 3 days per week for 3 months, under the delivery mode of either tele-exercise or a community-based approach. The community-based group will serve as a positive control as the effectiveness of the OEP to prevent falls is well established [24] and the aims of the current study focus on the effectiveness of the new mode of delivery, i.e. tele-exercise. The exercise programme will be structured with a warm-up, Otago strengthening and balance retraining exercises, “workouts on-demand” and cool down (Table 2). The OEP consists of five warm-up exercises (head movement, neck movement, back extension, trunk movement and ankle movement) and 17 strength and balance exercises [14]. For the “workouts on-demand” part, participants will express their needs such as focusing more on the upper body, flexibility, or strength. The instructor will present real-time demonstrations to promote exercise empowerment. Both groups of participants will be divided into classes of 9–10 people. In addition, they will be asked to maintain their daily number of steps at 10,000 or increase their step count by 3,500 compared with their usual habit. They will be required to record all the exercises they perform, the number of steps achieved and the fall incidence during the 12 months.

**Table 2 Tab2:** Lesson plan for both TE and CB groups

Content	Duration
Warm-up (dynamic and static stretching)	~ 10 min
A short pause to allow participants to be ready for the next part and interact with the instructor	
Otago exercise programme-strengthening exercises	~ 10 min
A short pause to allow participants to be ready for the next part and interact with the instructor	
Otago exercise programme- balance retraining exercises	~ 10 min
Workouts on-demand allow participants to - express their opinions on the exercises - request targeted training for specific body parts at a higher or lower level	5–10 min
Cool down	~ 10 min

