Chinese version of Fall Efficacy Scale-International: This is a validated measurement of fall efficacy with 16 questions regarding confidence of fall prevention at different situations on a four-point scale ranging from “not at all concerned” to “very concerned”. The score ranges from 16 to 64 and a lower score indicates a low fear of falling [35]. A perceived fear of falling is defined as points ≥ 20 [36].History of falls and fall incidence: A fall is defined as “an unexpected event in which the participant comes to rest on the ground, floor, or lower level, with or without injury” [37]. The history of falls including number, circumstance and severity in the previous 12 months will be assessed at the baseline [17]. The participants will be required to record their fall incidence prospectively in their diaries. The project assistant will also contact the participants regularly to ensure that they record the correct information.Right-hand and left-hand grip strength: This measurement will be performed by using a hand dynamometer (Takei Scientific Instruments Co. Ltd, Tokyo, Japan). The participants will be instructed to stand with their elbow extended and squeeze the dynamometer as hard as they can. Three attempts for both hands will be allowed and the mean of three scores will be counted [16].6-metre walk test: This is the test to assess the gait speed of the participants. The participants will be asked to walk as fast as possible without running for 10 m, which comprises a 2-metre approach, 6 m for time measurement and 2 m beyond the measurement. The units of this measurement are in seconds and will be divided by 6 to calculate the gait speed in m/s. Two attempts will be allowed and the mean of two scores will be counted [17].SARC-CalF: This is used to screen sarcopenia. It consists of six components namely strength, assistance in walking, rising from a chair, climbing stairs, falls and calf circumference [38, 39]. According to the Asian Working Group for Sarcopenia 2019 [27], diagnosis of possible sarcopenia includes SARC-CalF ≥ 11, handgrip strength (M:<28 kg, F < 18 kg) and 6-metre walk test < 1.0 m/s.Timed Up and Go Test: This is a test of functional lower-limb mobility. The participants will be seated with arms resting on the armrests. They will be asked to walk for 3 m, return to the chair, and sit down again. The time will be counted from standing to sitting back on the chair. Three attempts will be allowed and the mean of three scores will be counted [16].Berg Balance Scale score: This is a valid and reliable scale consisting of 14 static and dynamic balance activities. The score of each activity ranges from 0 to 4 and the total score ranges from 0 to 56 [40].Functional Reach Test: This test is used to assess dynamic bilateral stance balance. A metre ruler is fixed on the wall at participants’ shoulder height and the participants will be asked to stand next to but not touching the wall. The arm near the wall needs to be raised at 90° flexion and the third finger will be the initial position along the metre ruler. The participants will be asked to reach as far as possible without taking a step, bending their knees or falling over. The end position on the ruler will be marked. Three attempts will be allowed and the mean of three scores will be counted [17].Skeletal muscle mass and fat mass: The participants will be asked to dress in light clothing, hold the handgrips and stand still barefoot on a bioimpedance analyzer (Inbody 230, Biospace Co., Ltd, Seoul, Korea) after overnight fasting. The InBody 230 is a segmental impedance device which uses a tetrapolar 8-point tactile electrode method and two different frequencies (2 and 100 kHz). Fat mass, fat-free mass, percentage body fat and appendicular muscle mass (muscle mass of both arms and legs) are determined by the manufacturer’s algorithm of InBody 230. The appendicular skeletal muscle mass index (ASMI), expressed in kg/m^2^, is calculated by dividing the appendicular muscle mass by the square of height [41].

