### Statistical analysis

Descriptive data of the two groups including age, risk of falls, body mass index, muscle mass, and activity level at the baseline will be analyzed by independent t-test to test the homogeneity of the physical characteristics between the two groups. We will use an intention-to-treat analysis based on all randomized participants following the guidelines on randomized controlled trials [43]. We will perform a sensitivity analysis for missing data. The Kolmogorov-Smirnov one-sample test will confirm the normal distribution of all the measurement variables. A two-way repeated measures ANOVA will be performed for all the outcome measures, accounting for the group (TE and CB) and the interaction term between group and time. The p-value will be set at 0.05 for all tests. All statistical analyses will be carried out using SPSS, version 26.0 (IBM Co., Armonk, NY) by an independent statistician who will not be involved in the outcome assessment. Missing data will be complemented by using the multiple imputation method.

Both groups of participants will also be invited to attend focus group interviews with an experienced qualitative researcher. The Theory Domain Framework will be adopted to examine the determinants of behaviour change [44]. Data analysis will follow a framework approach [45] and use Qualitative Data Analysis (QDA) Miner 5 of Provalis Prosuite, which is qualitative data analysis software.

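### A serious in-class adverse event suspends the participant from the study, not just from the exercise sessions, so follow-up could be lost if the rule is applied literally and not lifted

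*Protocol article*

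**What the plan says.** The Adverse event reporting section of the protocol article describes two steps after a serious adverse event during class. The team investigates: "we will review the causes, the prescribed exercises, the course structure, and the safety precautions". Then: "The concerned participant will be suspended from the study". The article does not say how long the suspension lasts or which activities it covers.

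The other relevant rules are general and do not mention a suspended participant:

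- **Baseline assessment:** "Assessment will be performed before the intervention period, at the end of the 3rd, 6th and 12th months".
- **Interventions:** "All participants will attend the exercise training 3 days per week for 3 months". Participants also record their exercise, "the number of steps achieved and the fall incidence during the 12 months".
- **Primary outcomes:** on the falls diary, "The project assistant will also contact the participants regularly to ensure that they record the correct information".
- **Secondary outcomes:** dropout counts participants who "refuse to continue the training during the intervention phase or refuse to provide information during the maintenance phase".
- **Statistical analysis:** "We will use an intention-to-treat analysis based on all randomized participants". Missing data are to be multiply imputed, and a sensitivity analysis for missing data is planned.

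**The concern.** Stopping the exercise after a serious event is a safety decision and is not in dispute. Stopping observation is a different decision, and the sentence does not separate the two. A member of staff who follows it literally would stop assessing the participant and stop collecting the diary.

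The loss would be related to the outcome. Fear of falling, fall incidence, balance and mobility are all listed as primary outcomes, and the safety section for the tele-exercise arm uses a fall as its example of an incident. A person removed after such an event may well have worse later function and more falls than the participants whose data would inform the imputation.

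The number affected could also differ between arms, because one arm exercises at home with verbal correction only and the other face to face. The article gives no event rates, so this is only a possibility. The Discussion names safety while exercising at home as the team's major concern, so what happens to a person after a serious in-class event should be observed, not imputed.

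**Working it through.** The plan states no figure on this point. The check is therefore a reading of the text, followed by a calculation for scale.

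**Does any other section keep a suspended participant under follow-up?**

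1. The assessment schedule, the 12-month diary and the regular falls contact apply to participants in general. They make no exception for a suspended participant, but they do not say that one remains included. The adverse event sentence is the specific rule, and it refers to the study.
2. Intention-to-treat on all randomised participants defines who is analysed. Imputation and the sensitivity analysis deal with data that are already missing. None of these makes staff collect data.
3. The dropout definition covers refusal by the participant, so a suspension imposed by the team has no status there. It does list refusing training and refusing information as separate things, although both count towards one dropout rate.
4. Adverse events are recorded in both phases, so the event itself would still be recorded.

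**What is lost per affected person, if the suspension covers assessments and is not lifted?**

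- All classes fall in months 0 to 3, so the suspension comes before every follow-up assessment: 3 of 3 are lost.
- With an assumed equal split, 92 / 2 = 46 per arm. Planned follow-up assessments per arm are 46 × 3 = 138, and 3 / 138 = 2.2%.
- An event at the start leaves 12 of 12 diary months uncollected, and one at the end of month 3 leaves 12 − 3 = 9.
- If the suspension is only a pause in training, the loss is zero.

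**How far could one such person move the comparison?**

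Suppose one arm has one more suspended person than the other, and that person's true outcome is *d* SD worse than the imputed value. The arm mean, and so the difference, shifts by *d* / 46. Ignoring clustering, the standard error of the difference is √(2/46) = 0.2085 SD.

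| Assumed *d* (SD) | Shift = *d* / 46 (SD) | Shift / 0.2085 |
|---|---|---|
| 0.5 | 0.011 | 0.05 |
| 1.0 | 0.022 | 0.10 |
| 1.5 | 0.033 | 0.16 |

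The values of *d* are assumptions. The article gives neither *d* nor a rate of serious in-class events, so no expected bias can be computed.

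**The case against.** The strongest reply is that a suspension is ordinarily provisional. The article does not say withdrawn or excluded, and the sentence follows a promised review of the exercises and precautions, which fits a pause in training until the review is done. The general rules on assessments, diary and falls contact contain no exception, and the analysis is by intention to treat. This reading is reasonable and may be what is intended. It does not settle the matter, because the rule refers to the study and no section says that follow-up continues. Staff could fairly apply it either way.

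Four further points have some force:

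- **Return rule.** The conditions for resuming exercise may be set out in the full protocol or in the safety protocol, whose figure is not shown. Their absence from an article should carry no weight, and the point rests on the wording that is present.
- **Sensitivity analysis.** The planned analysis for missing data would help to show how far results depend on the imputation, but it cannot recover assessments that were never made.
- **Dropout definition.** It is weak support, since it does not say that a person who stops training stays in follow-up.
- **Size.** The Discussion describes adverse events with this exercise programme as relatively infrequent, and equal numbers of suspensions in the two arms would roughly cancel. No planned test or conclusion is shown to change. This stands in full, and it is why the point ranks low.

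**Conclusion.** The concern holds as a badly worded rule of low severity. Applied literally and not lifted, it would create avoidable, outcome-related missing data in the population that the protocol undertakes to analyse. Each affected person would lose 3 of 3 follow-up assessments and 9 to 12 of 12 diary months. If only a training pause is meant, nothing is lost.

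The likely effect on the group comparison is very small: about 0.02 SD (0.01 to 0.03 SD) per excess suspended person, or 0.10 (0.05 to 0.16) of the standard error. This rests on 46 per arm, an assumed gap of 1 SD (0.5 to 1.5 SD) between true and imputed outcomes, and no allowance for randomisation by centre. The main benefit of a change is that staff act in one way and that the person who had the event remains under observation.

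**What to change.** Reword the sentence under Adverse event reporting along these lines: after a serious adverse event during class, the participant is suspended from the exercise sessions only, and resumption is decided by the clinicians who oversee medical clearance and safety (named under Data monitoring and quality control). Add that the fall diary and the 3-, 6- and 12-month assessments continue if the participant is willing, and that the participant is analysed in the allocated arm.

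The cost is a sentence or two of protocol text. Because the trial is running and has ethics approval, a minor amendment and a note to staff are likely to be needed. No visits are added beyond those already planned for that participant. Trial Status reports three groups in the intervention phase and five still to be recruited, so the change can still apply to most of the trial.

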### Statistical analysis

Descriptive data of the two groups including age, risk of falls, body mass index, muscle mass, and activity level at the baseline will be analyzed by independent t-test to test the homogeneity of the physical characteristics between the two groups. We will use an intention-to-treat analysis based on all randomized participants following the guidelines on randomized controlled trials [43]. We will perform a sensitivity analysis for missing data. The Kolmogorov-Smirnov one-sample test will confirm the normal distribution of all the measurement variables. A two-way repeated measures ANOVA will be performed for all the outcome measures, accounting for the group (TE and CB) and the interaction term between group and time. The p-value will be set at 0.05 for all tests. All statistical analyses will be carried out using SPSS, version 26.0 (IBM Co., Armonk, NY) by an independent statistician who will not be involved in the outcome assessment. Missing data will be complemented by using the multiple imputation method.

Both groups of participants will also be invited to attend focus group interviews with an experienced qualitative researcher. The Theory Domain Framework will be adopted to examine the determinants of behaviour change [44]. Data analysis will follow a framework approach [45] and use Qualitative Data Analysis (QDA) Miner 5 of Provalis Prosuite, which is qualitative data analysis software.

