**Methods:**

The primary objective is to evaluate the effectiveness of tele-exercise (TE) in relation to physical functioning and exercise adherence among community-dwelling older people at risk of falls in comparison with a community-based group (CB). The secondary objective includes evaluating older people’s experience with tele-exercise, emphasizing their psychological welfare, social well-being, and acceptance of the telehealth approach. The design, conduct, and report follow the SPIRIT guidelines (Standard Protocol Items: recommended items to address in a Clinical Trial Protocol and Related Documents). Older people will be recruited from 10 local community centres in Hong Kong and randomly allocated into two groups. All participants will attend the exercise training 3 days per week for 3 months but the mode of delivery will differ, either online as the tele-exercise group (TE) or face-to-face as the community-based group (CB). The outcome measures include muscle strength, physical function, exercise adherence and dropout rate, psychological and social well-being will be assessed at the baseline, and the 3rd, 6th and 12th month. Some participants will be invited to attend focus group interviews to evaluate their overall experience of the tele-exercise training.

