### Randomization and blinding

After the screening phase, ten community centres will be coded and then randomized such that a similar number of centres will be allocated to either the tele-exercise group (TE) or community-based group (CB) in a concealed, blinded fashion to minimize cross-over contamination between the groups. An independent assistant will oversee the randomization procedures and allocation sequence. Around ten participants will be recruited from each centre. The assessments will be performed by trained outcome assessors who will be blinded to the group assignments. It is impossible to blind the participants in the training mode. However, they cannot communicate with other groups of participants because they are recruited from different locations. The instructors and researchers will not be blinded and will be asked to refrain from discussing the group assignments of the participants with the outcome assessors.

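### Ten community centres are randomised, but every outcome is analysed with an individual-level repeated measures ANOVA that ignores centre, so p-values are too small and any intervals too narrow

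*Protocol article*

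**What the plan says.** Under *Randomization and blinding* the protocol article makes the centre the unit of allocation: "ten community centres will be coded and then randomized such that a similar number of centres will be allocated" to tele-exercise (TE) or community-based training (CB), in order to limit contamination. It adds: "Around ten participants will be recruited from each centre". Under *Interventions*: "Both groups of participants will be divided into classes of 9–10 people". *Trial Status* counts progress in groups: two CB groups finished, one CB and two TE groups under way and five still to be recruited, which makes ten. One class per centre is not stated outright, but these three sections all fit it.

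The abstract (*Methods*) describes the design differently: "Older people will be recruited from 10 local community centres in Hong Kong and randomly allocated into two groups".

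*Statistical analysis* commits to a specific model: "A two-way repeated measures ANOVA will be performed for all the outcome measures, accounting for the group (TE and CB) and the interaction term" (that is, group-by-time). Baseline characteristics are compared by independent t-tests, the significance level is 0.05 throughout, and the analysis set is described thus: "We will use an intention-to-treat analysis based on all randomized participants". Missing values are to be filled by multiple imputation. The article nowhere mentions an ICC, a design effect, a random effect or robust standard errors, and *Sample size calculation* has no allowance for clustering.

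**The concern.** The analysis has to respect the unit that was randomised. Here that unit is the centre, so the comparison of TE with CB rests on ten independent units, about five per arm. The planned ANOVA judges the arm difference against variation between individuals, as if each person had been allocated separately.

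Two kinds of centre variation matter. Stable differences between centres (membership, neighbourhood, general fitness) enter the group main effect. Differences between centres in how people change enter the group-by-time effect. These could arise because a class trains together three times a week and part of each lesson follows what its members ask for. Where either kind exists, the corresponding standard error is too small.

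A difference between delivery modes, in either direction, could then be declared from centre variation alone. The *Background* hypothesis is that tele-exercise works as well as the usual format. Any interval from this model used to support that hypothesis would be too narrow. The model is named for all outcome measures, so every primary outcome is affected.

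**Working it through.** **Inputs from the protocol.** Ten centres; 92 participants in total, so 92/10 = 9.2 per centre; four assessments (baseline, 3, 6 and 12 months); alpha 0.05.

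**Assumptions.** Five centres per arm (the protocol says only that the numbers will be similar). ICC from 0.02 to 0.10, since none is given.

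**The plan's own figure.** The protocol's 92 is used here only to obtain the centre size. It cannot be uniquely reproduced, because neither the G*Power test nor the type of effect size (d or f) is stated. Nothing below depends on how it was derived. The figure at issue is the nominal 5%.

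**Degrees of freedom.** Between arms: 10 − 2 = 8, with critical t = 2.306. The individual-level test uses 92 − 2 = 90, with critical t = 1.987.

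**Group comparison, by formula.** Design effect DE = 1 + (m − 1) × ICC with m = 9.2. True false-positive rate ≈ 2 × [1 − Φ(1.96/√DE)]. Effective sample size = 92/DE. The simulated column uses an individual-level test under the null with 10 centres of 9.

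| ICC | DE | √DE | Rate, formula | Rate, simulated | Effective n |
|---|---|---|---|---|---|
| 0.02 | 1 + 8.2 × 0.02 = 1.16 | 1.079 | 6.9% | 7.0% | 79 |
| 0.05 | 1 + 8.2 × 0.05 = 1.41 | 1.187 | 9.9% | 9.9% | 65 |
| 0.10 | 1 + 8.2 × 0.10 = 1.82 | 1.349 | 14.6% | 14.4% | 51 |

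In the same simulations the rate with no clustering was 4.9%. A t-test on ten centre means (8 df) stayed at 4.9% to 5.1% throughout.

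**Interval width.** Relative to the individual-level interval, a correct one is wider by about √DE × 2.306/1.987 = √DE × 1.161. That gives 1.25, 1.38 and 1.57 at ICC 0.02, 0.05 and 0.10.

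**The planned four-time ANOVA.** This was simulated under the null: 10 centres of 9, participant variance 0.6, residual variance 0.4, 4,000 runs per row.

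| Stable centre variance | Centre-by-time variance | Group test | Group-by-time test |
|---|---|---|---|
| 0 | 0 | 5.3% | 4.9% |
| 0.02 | 0 | 7.4% | 5.3% |
| 0.05 | 0 | 11.6% | 5.3% |
| 0 | 0.01 | 5.8% | 9.2% |
| 0 | 0.02 | 5.6% | 13.2% |
| 0.02 | 0.02 | 8.2% | 12.3% |
| 0.05 | 0.05 | 12.5% | 25.1% |

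A stable centre effect inflates the group test and cancels from the interaction. A centre-by-time effect inflates the interaction, and small amounts of it are enough.

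**The case against.** The mismatch between the allocation and the model is hard to dispute. The serious objections concern its size and consequences.

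- *The primary outcomes are changes over time, so group-by-time is the key test, and a stable centre effect drops out of it.* This is correct. The 7% to 14% range illustrates the group term only. For the interaction, the relevant ICC is that of change scores, and the protocol gives nothing on it.
- *Class effects may be small.* One instructor leads all classes, both arms share one lesson plan, and exercise level is tailored to the individual. TE participants train at home without seeing one another. These features limit correlation that arises in class, especially in TE. They do not remove differences between centres in membership or neighbourhood, or in how people change over the following nine months.
- *No confidence intervals are promised.* True. The point about intervals applies to any that are later derived from this model.
- *False differences work against a hypothesis of equal effectiveness.* Also true if equality is inferred from a non-significant test. The error is then a spurious difference, which is still a wrong result. If an interval is used instead, the error favours the hypothesis.
- *The content of an imputation model is normally left to the SAP.* Agreed. The protocol's silence there is not counted as a fault, and centre appears below only as a consequence of the fix.

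None of this is detail left for later. The article names the model for every outcome, and that model does not match its own allocation.

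**Conclusion.** The concern holds. As written, the analysis treats participants as the randomised units although centres are randomised, so its stated 5% error rate is not assured. For the group effect the true rate is about 7%, 10% and 14% at ICC 0.02, 0.05 and 0.10. For group-by-time it stays near 5% if centres differ only in level, and reaches about 9% to 13% with centre-by-time variances of 0.01 to 0.02. These figures rest on an assumed ICC range, five centres per arm, about nine people per centre and the variance split shown. Another ICC would change the size of the error but not its direction. It should be corrected before the analysis. At the reported status five of the ten groups were still to be recruited, so the plan could be corrected in time.

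**What to change.** Describe the trial as cluster-randomised in the abstract, *Methods/design* and *Statistical analysis*, and define the intention-to-treat set as all participants of the randomised centres. Replace the ANOVA with one of the following:

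- a linear mixed model with group, time and group-by-time as fixed effects, random effects for centre, centre-by-time and participant, and Satterthwaite or Kenward-Roger degrees of freedom; or
- one summary per centre for each outcome (for example, mean change from baseline), compared by a t-test on 8 df.

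With only ten centres the random centre effects may be poorly estimated. The centre-level analysis is then sufficient, and the plan should say in advance which one governs. Whichever is chosen, centre should also be in the imputation model, and individual-level baseline p-values should not be relied on.

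No new data are required, only revised wording and a different procedure. The cost is precision: intervals about 1.25 to 1.57 times as wide over the assumed ICC range. Power for a single-time comparison falls too. After 20% attrition (about 7.4 per centre, 74 in all), if the protocol's 0.367 is an f (d = 2 × 0.367 = 0.734), a centre-level test has 74%, 67% and 58% power at ICC 0.02, 0.05 and 0.10. The individual-level calculation gives 88%. If 0.367 is a d, the centre-level figures are 26%, 23% and 19%, against 35%. The sample size section should state this loss.
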